## Abstract

**Rationale::**

Evidence about long-term sequelae after hospitalization for acute respiratory distress syndrome due to COVID-19 is still scarce.

**Purpose::**

To evaluate changes in pulmonary, cardiac, and renal function and in quality of life after hospitalization for acute respiratory distress syndrome secondary to COVID-19.

**Methods::**

This will be a multicenter case–control study of 220 participants. Eligible are patients who are hospitalized for acute respiratory distress syndrome due to COVID-19. In the control group, individuals with no history of hospitalization in the last 12 months or long-term symptoms of COVID-19 will be selected. All individuals will be subjected to pulmonary spirometry with a carbon monoxide diffusion test, chest tomography, cardiac and renal magnetic resonance imaging with gadolinium, ergospirometry, serum and urinary creatinine, total protein, and urinary microalbuminuria, in addition to quality-of-life questionnaires. Patients will be evaluated 12 months after hospital discharge, and controls will be evaluated within 90 days of inclusion in the study. For all the statistical analyses, p < 0.05 is the threshold for significance.

**Results::**

The primary outcome of the study will be the pulmonary diffusing capacity for carbon monoxide measured after 12 months. The other parameters of pulmonary, cardiac, and renal function and quality of life are secondary outcomes.

**Conclusion::**

This study aims to determine the long-term sequelae of pulmonary, cardiac, and renal function and the quality of life of patients hospitalized for acute respiratory distress syndrome due to COVID-19 in the Brazilian population.

## INTRODUCTION

The pulmonary pathology caused by severe acute respiratory syndrome coronavirus 2 (SARS-CoV-2) has resulted in a substantial increase in the demand for ventilatory assistance and long stays in intensive care units (ICUs).^(1)^ The initial data indicate that approximately 15% of patients affected by SARS-CoV-2 require hospitalization, and about 3% will require intensive care.^(2)^ Coronavirus disease 2019 (COVID-19) is estimated to have caused more than 12 million ICU admissions worldwide.^(3)^

Acute respiratory distress syndrome (ARDS) is the most feared pulmonary complication related to COVID-19 due to its association with a long hospital stay and mortality.^(4)^ Approximately 42% of patients with COVID-19 pneumonia develop ARDS, and 60-80% require intensive care.^(5)^ Acute respiratory distress syndrome is an inflammatory process resulting from local or systemic injury to the pulmonary alveolar-capillary membrane, causing an increase in local vascular permeability, with subsequent interstitial and alveolar edema.^(6)^ Even if patients are discharged from the hospital, ARDS survivors are at high risk of persistent physical disability.^(7)^ Prepandemic studies have shown that ARDS survivors have reduced muscle function, with a high prevalence of physical-functional disability, restrictive ventilatory disorder, and decreased pulmonary diffusion.^(8–10)^ In one study 39% of ARDS survivors exhibited critically ill polyneuropathy, their physical weakness lasting for up to 12 months after hospital discharge.^(7)^ Despite the predominant respiratory involvement, several reports have identified additional direct or indirect involvement of the cardiovascular and renal systems.^(11–14)^ These acute insults can lead to long-term organ dysfunction, reducing quality of life and necessitating follow-up and treatment of sequelae over a longer period.^(15)^

According to the World Health Organization,^(16)^ detecting any causal link between COVID-19 and long-term sequelae is a research priority. Evidence on the prevalence of pulmonary, cardiovascular, and renal sequelae in survivors of ARDS due to COVID-19 in the Brazilian population is still scarce. We present the study protocol for the Post-COVID-19 Brazil 3 study, with a focus on analyzing the impact on pulmonary, cardiac, and renal functions, as well as quality of life, among ARDS survivors with COVID-19 starting 12 months after discharge.

## METHODS

This is a prospective, multicenter case–control study of patients who survived hospitalization for COVID-19 and were diagnosed with ARDS and controls without persistent symptoms of COVID-19 and hospitalization due to clinical disease in the last 12 months. The study design is summarized in figure 1. The study protocol is registered at Clinicaltrials.gov (NCT05225194). This study was approved by the National Research Ethics Committee (Conep) (CAAE: 54943222.7.1001.5330) and adheres to resolution 466/12 of the National Health Council (CNS) of Brazil. Free and informed consent will be obtained from all participants.

**Figure 1 f1:**
[figure not shown]
Study design.

### Patient selection

#### Patients with acute respiratory distress syndrome

Patients will be considered eligible if they are ≥ 18 years of age, have a positive reverse transcription polymerase chain reaction (RT-PCR) test or a positive antigen test for SARS-CoV-2 infection collected via nasopharyngeal swab during hospitalization or within 14 days beforehand, and are diagnosed with ARDS due to COVID-19 during hospitalization, and hospital discharge from the index hospitalization. The diagnosis of ARDS was defined according to the Berlin criteria:^(17)^ respiratory failure not fully explained by heart failure or fluid overload; onset within one week of the known lesion or new symptoms that worsened; bilateral opacities not fully explained by effusions, lobar collapse, lung collapse, or nodules; hypoxemia defined as the relationship between partial pressure of oxygen and fraction of inspired oxygen (PaO_2_/FiO_2_) ≤ 300mmHg, with positive end-expiratory pressure or continuous positive airway pressure ≥ 5cmH_2_O. The exclusion criteria are severe underlying disease with a life expectancy less than 3 months, unwillingness to undergo the tests to be performed, absence of a family member if the patient has communication difficulties (aphasia, cognitive impairment, nonnative speakers of Portuguese), and nonconsent to participate in the study.

#### Controls

Individuals ≥ 18 years of age who are family members or social interactors of participants who have survived ARDS due to COVID-19 will be considered controls. Individuals who are unwilling to undergo the proposed tests, have a history of persistent symptoms after SARS-CoV-2 infection, have a history of nonelective hospitalization due to clinical disease in the last 12 months, have a severe underlying disease with a life expectancy of less than 3 months, or do not consent to participate in the study will be ineligible. The following symptoms are considered persistent symptoms of COVID-19: cough, fatigue, muscle pain, dyspnea, anosmia, ageusia, and memory or concentration deficit, as previously evaluated by a physician and attributed to COVID-19.

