### Recruitment

The patients will be recruited from hospitals located in the city of Porto Alegre and its metropolitan region. Patients with ARDS will be accessed from outpatient clinics, databases, or previous records of ICU admission due to ventilatory failure of patients undergoing clinical follow-up at the respective centers, and controls will be recruited from family members or people living with the patients. Telephone contacts will be made after hospital discharge, and the eligibility criteria and the free and informed consent form will be applied. With duly informed and signed consent, the following procedures will be performed: a review of medical records and structured telephone interviews and teleconsultation to assess eligibility and scheduling of previously specified exams.

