### Calculation of sample size

A sample size of 198 individuals (99 for each group) was calculated to detect a minimum clinically relevant difference of 2mL/minute/mmHg in the mean DLCO between the COVID-19 ARDS patients and healthy controls. Factoring in a 10% rate of losses and refusals, we will need 110 in each group given a desired power of 80%, a significance level of 5%, and a standard deviation of 5mL/minute/mmHg.

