### Statistical analysis

The variables will be described as n (%) for qualitative variables, mean ± standard deviation for symmetric quantitative variables, and median (interquartile range) for asymmetric quantitative variables. The distribution of quantitative variables will be assessed by graphical visualization of histograms and the Shapiro–Wilk test. The primary outcome will be compared between the study groups using logistic regression adjusted for sex, age, and comorbidities. The reported measure of effect will be the odds ratio (OR) with its 95% confidence interval (95%CI). The secondary outcomes with qualitative distributions will be evaluated in the same way as the primary outcome. The quantitative distribution of secondary outcomes will be evaluated by means of multiple linear regression adjusted for sex, age, and comorbidities. The reported measure of effect will be the difference in means with their 95%CIs. P values < 0.05 will be considered statistically significant. Secondary outcomes will not be adjusted for multiple variables. Thus, the findings for the secondary outcomes will be interpreted as exploratory. The analyses will be performed with R software packages to be detailed at the time of analysis.^(25)^

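### Controls are drawn from the patients' own families and contacts, but the named models and the sample size take no account of that link; if outcomes stay correlated within families, standard errors will generally be off, mostly on the conservative side

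*Protocol article*

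**What the plan says.** The link between controls and patients is part of the definition of a control. Under Controls, adults "who are family members or social interactors of participants who have survived ARDS due to COVID-19 will be considered controls". The first Recruitment section repeats this in slightly different terms: "controls will be recruited from family members or people living with the patients". The number of controls per patient is not given, and neither section describes matching.

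The Statistical analysis section then names the models. For the primary outcome: "The primary outcome will be compared between the study groups using logistic regression adjusted for sex, age, and comorbidities". Qualitative secondary outcomes follow the same route. For the others: "The quantitative distribution of secondary outcomes will be evaluated by means of multiple linear regression adjusted for sex, age, and comorbidities". No pair or family term, random effect, GEE or cluster-robust standard error is mentioned.

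The Calculation of sample size section plans for a "minimum clinically relevant difference of 2mL/minute/mmHg in the mean DLCO" with "a standard deviation of 5mL/minute/mmHg", 80% power and a 5% significance level. This gives 99 per group, or 110 after 10% losses.

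**The concern.** People who share a household or family may share smoking exposure, living conditions and, for blood relatives, genes. Such factors can plausibly affect lung diffusion, exercise capacity and quality of life, and adjustment for sex, age and comorbidities need not remove them. A regression with its usual model-based standard errors assumes that no such correlation is left.

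Two effects then pull in opposite directions. Positive correlation between a patient and that patient's control makes the difference between groups less variable than the model believes, so intervals are too wide and power is lost. Correlation among several controls from one family makes the control mean more variable than the model believes, so intervals are too narrow. At stake are the coverage of the 95% intervals and precision that the design offers at no extra recruitment.

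**Working it through.** **Inputs from the protocol article (Calculation of sample size):** difference 2, SD 5 (mL/min/mmHg), alpha 5% (taken as two-sided), power 80%, 99 per group, 10% losses.

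**Assumed, because the documents give no value:** a residual within-family correlation rho of 0.1, 0.2 or 0.3, and the linkage patterns below.

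**1. The plan's own figure.** For two independent means, n per group = 2 × [5 × (1.960 + 0.842) / 2]² = 98.1, rounded up to 99. Then 99 / 0.9 = 110. Both figures reproduce under independence, so the linkage played no part in the planning.

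**2. One analysed control per analysed patient, 99 pairs.**
- SE under independence: 5 × √(2/99) = 0.711.
- True SE: 5 × √(2(1 − rho)/99).
- Ratio of the two: 1/√(1 − rho).
- Actual alpha: 2 × P(Z > 1.96 × ratio).
- Power if the link is ignored: Φ[(2 − 1.96 × 0.711) / true SE].
- Power if the link is used: Φ[2 / true SE − 1.96].

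| rho | True SE | Ratio | Actual alpha | Power, link ignored | Power, link used |
|---|---|---|---|---|---|
| 0 | 0.711 | 1.000 | 5.0% | 80% | 80% |
| 0.1 | 0.674 | 1.054 | 3.9% | 82% | 84% |
| 0.2 | 0.636 | 1.118 | 2.8% | 83% | 88% |
| 0.3 | 0.595 | 1.195 | 1.9% | 85% | 92% |

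**3. Partial linkage.** If only a fraction f of controls is effectively linked to an analysed patient, the ratio is 1/√(1 − f × rho). With f = 0.5 it is 1.026, 1.054 and 1.085 for the three correlations, and alpha is 4.4%, 3.9% and 3.4%.

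**4. Several controls per family, index patient analysed.** With equal groups and m controls in each linked family, the variance of the difference is (SD²/n) × [1 + 1 + (m − 1)rho − 2rho] = (SD²/n) × [2 + (m − 3)rho].
- m = 1 gives 2 − 2rho, as in step 2.
- m = 2 gives 2 − rho. The independence SE is still too large, by a factor of 1.026 to 1.085.
- m = 3 gives exactly 2. The two effects cancel and the independence SE is right.

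**5. Several controls per family, index patient not analysed.** The offsetting covariance disappears and the variance factor becomes 2 + (m − 1)rho.
- m = 2: ratio 0.976 to 0.933, alpha 5.6% to 6.8%.
- m = 3: ratio 0.953 to 0.877, alpha 6.2% to 8.6%.

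Over these two cases the SE is about 2% to 12% too small. The pattern is possible for individual outcomes, because the Procedures section keeps participants who cannot undergo one or more exams.

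**The case against.** The strongest reply is that the article is a condensed account. It never states that errors are independent, and an analysis plan that is not shown could add robust or clustered standard errors. That is possible and limits the weight of the point. It does not remove it, because the article does fix the type of regression, the covariates and the effect measures, and the planning figure reproduces only as a comparison of independent groups. As written, this is a stated method that passes over a dependence built into the design.

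Other objections stand, and they rule out stronger readings that a reader might infer:

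- *The standard errors are certainly wrong.* Not supported. At zero residual correlation there is no error, and the documents give no correlation. Controls may also be social contacts with little in common with the patient, and one-to-one linkage is not stated; equal group sizes do not create pairs.
- *Whatever the linkage pattern, the 95% intervals miss their stated coverage.* Not so. With three controls per analysed patient the two effects cancel exactly in step 4.
- *The trial is too small.* In the one-to-one case, power with the link ignored is 82% to 85%, above the planned 80%. The loss is measured against a better analysis, not against the trial's target.
- *The figures describe the primary analysis.* They describe an unadjusted difference in mean DLCO, the scale of the sample size calculation. The planned primary measure is an adjusted odds ratio, whose standard error and power were not computed here.

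**Conclusion.** The point holds in conditional form. Controls are linked to enrolled patients by definition, while the named models and the sample size make no use of the link. If residual within-family correlation is not zero, the model-based standard errors will generally be off, by an amount and in a direction that depend on the linkage pattern.

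The most natural pattern, one control per patient with positive correlation, is conservative: validity is not threatened, but 2.7 to 7.4 percentage points of power go unused at correlations of 0.1 to 0.3. Anti-conservative inference needs a more particular pattern, such as several controls from a family whose patient is missing from that analysis. All sizes rest on the assumed correlations and on the mean-difference scale. This is a worthwhile, inexpensive improvement in precision and interval validity, not a flaw that undermines the planned 80% power or the 110 per group.

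**What to change.** - Record for each control the study ID of the linked patient, and define the cluster as the family or household. Store it as a coded field that survives the anonymised extraction described under Data security; otherwise the link may not reach the analysis file.
- State how many controls may be enrolled per patient.
- Keep the planned covariates and fit the models by GEE with cluster-robust standard errors on that cluster, for both binary and quantitative outcomes. For quantitative outcomes a random family intercept is an alternative. The GEE form has the advantage that its standard errors remain valid for either sign of the correlation.
- Treat participants without an analysed relative or contact as clusters of one, so that nobody is dropped.

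The cost is one extra database field and a slightly more complex model statement. No additional participants, visits or exams are needed. The field is best added while recruitment is open, since links are harder to reconstruct afterwards.

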### Procedures

All participants will undergo teleconsultation by telephone to evaluate possible contraindications for the following complementary exams: serum creatinine and urea, creatinine and total protein in urine, microalbuminuria and qualitative urinalysis; spirometry with pulmonary diffusion for carbon monoxide (CO_2_) without a bronchodilator test; treadmill ergospirometry with a ramp protocol; high-resolution tomography of the chest (noncontrast); and cardiac and renal magnetic resonance imaging with gadolinium contrast. Patients with contraindications to one or more exams who are eligible will remain in the study. Teleconsultation and exams will be performed between 12 and 36 months after discharge from the index hospitalization for ARDS or, for controls, at the time of inclusion (with a restricted window of up to 90 days due to the risk of controls developing COVID-19 or other clinical complications after the initial visit). Figure 2 is the flow chart of the participants in the study.

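### The 12-month look-back for controls does not bar people hospitalized with COVID-19, even with ARDS, more than a year ago, although patients are themselves examined 12 to 36 months after discharge

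*Protocol article*

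**What the plan says.** The Controls section draws controls from the patients' own circle: "family members or social interactors of participants who have survived ARDS due to COVID-19 will be considered controls". Two of its exclusions bear on earlier COVID-19:

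- **Hospitalization.** Ineligible are people who "have a history of nonelective hospitalization due to clinical disease in the last 12 months".
- **Symptoms.** Ineligible are people who "have a history of persistent symptoms after SARS-CoV-2 infection". The section then lists the symptoms that count and restricts them to those "as previously evaluated by a physician and attributed to COVID-19".

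The 12-month limit is not a slip in one place. The opening of Methods describes "controls without persistent symptoms of COVID-19 and hospitalization due to clinical disease in the last 12 months", and the Abstract says that "individuals with no history of hospitalization in the last 12 months or long-term symptoms of COVID-19 will be selected".

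For the patients, Procedures states: "Teleconsultation and exams will be performed between 12 and 36 months after discharge from the index hospitalization for ARDS". The sample size section frames the intended contrast as a difference of "2mL/minute/mmHg in the mean DLCO between the COVID-19 ARDS patients and healthy controls".

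**The concern.** The two time windows do not overlap. Every patient's qualifying stay ended at least 12 months before the examination, while the control rule looks only at the most recent 12 months. The control rule therefore cannot see an admission of the same kind and age as the one that defines the patient group. As written, one person could satisfy the criteria for both groups.

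The setting makes this more than theoretical. Controls are relatives, household members or social contacts of people who had severe COVID-19, so infection in the same period is plausible. The Discussion adds that the patients may come from early in the pandemic, and their contacts' admissions could be just as old.

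Former COVID-19 inpatients in the control group would move its DLCO, imaging and renal results toward those of the patients. The estimated difference shrinks and power falls. Adjustment for sex, age and comorbidities does not correct for a control who has had the condition under study.

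**Working it through.** **Step 1: compare the criteria.** Take a household contact discharged after COVID-19 ARDS 20 months ago, now without symptoms or with symptoms no physician ever attributed to COVID-19.

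| Control criterion | Does it exclude this person? |
|---|---|
| Nonelective hospitalization in the last 12 months | No, it was 20 months ago |
| Persistent symptoms, physician-attributed | No |
| Life expectancy under 3 months | No |
| Unwilling to be tested, or no consent | No |

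With a positive swab result from that time, the same person could meet the ARDS patient criteria and falls inside the 12 to 36 month examination window.

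**Step 2: reproduce the plan's sample size.** Inputs from the sample size section: difference 2 mL/min/mmHg, SD 5, power 80%, significance level 5% (two-sided assumed; the section does not say), equal groups.

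- n per group = 2 × (1.960 + 0.842)² × 5² / 2² = 98.1, rounded up to 99. This matches the plan.
- Allowance for losses: 99 / (1 − 0.10) = 110 per group, 220 in total. This also matches.
- Two-sample t-test power at 99 per group: noncentrality 2 / (5 × √(2/99)) = 2.814, power 80.0%.

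**Step 3: let a fraction f of controls carry the full patient-group deficit.** The expected difference becomes 2 × (1 − f), with the SD held at 5. The documents give no value for f, so a range is shown.

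| f (assumed) | Expected difference (mL/min/mmHg) | Power, 99 per group |
|---|---|---|
| 0% | 2.00 | 80.0% |
| 1.5% | 1.97 | 78.8% |
| 3% | 1.94 | 77.5% |
| 5% | 1.90 | 75.8% |
| 10% | 1.80 | 71.2% |
| 20% | 1.60 | 61.0% |

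If all 110 per group were evaluable, power at f = 3% would be 81.7%.

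**Step 4: anchor f in the article's own figures.** The Introduction says that about 15% of people affected by SARS-CoV-2 need hospital care and about 3% need intensive care. If every control had been infected, and intensive care is taken as a rough proxy for ARDS, f is about 3%. If half had been infected, f is about 1.5%. The Introduction also says that about 42% of patients with COVID-19 pneumonia develop ARDS. If every hospitalized person had pneumonia, that gives 0.15 × 0.42 = 6.3%, which lies between the 5% and 10% rows. These are ceilings in two respects: they assume that all controls were infected and that the symptom exclusion removes none of them. A value of 20% exceeds even the whole hospitalized share.

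**The case against.** The strongest reply is that the gap in the wording will rarely matter.

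- **The symptom exclusion has no time limit.** People once hospitalized with COVID-19 are plausibly the most likely to have had symptoms assessed by a physician, so the filter should work best for them. Those who pass it are relatively well and may not carry the full DLCO deficit. This stands as a reason to expect a small effect. It does not close the gap, because DLCO, CT and MRI can be abnormal without attributed symptoms.
- **Screening may reveal such people.** Recruitment includes record review, interview and teleconsultation, and baseline collection covers previous health information. This makes undetected enrolment less likely. But discovering an old admission does not make the person ineligible under the stated rule, and detailed data on the COVID-19 hospitalization are specified only for the ARDS group.

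Three stronger readings are tempting and are not supported:

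- A reader might infer that controls were meant to be unexposed to the virus. The article does not say so: past infection without persistent symptoms is allowed by design. The defect is confined to earlier COVID-19 hospitalization or ARDS.
- A reader might take the 61% row as the likely power. Nothing in the documents supports 20% of controls carrying a full ARDS deficit.
- A reader might want to bar anyone with respiratory failure of any cause at any time. The ARDS patient criteria place no such limit on earlier history, so this one-sided restriction would favour healthier controls and could bias the difference away from zero.

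**Conclusion.** The concern holds as a defect in the stated control criteria. Under the rule as written, a contact hospitalized with COVID-19, even with ARDS, more than 12 months ago can be enrolled as a control if no persistent symptoms were attributed to COVID-19 by a physician.

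The bias is toward zero. Its size is unknown and probably modest: at an assumed 3% of controls with the full deficit, a loss of about 2.5 percentage points of power (80.0% to 77.5%); at 5%, about 4 points. Fractions of 10% or more are extreme. These figures rest on an assumed fraction, a full deficit in each such control, SD 5, a two-sided 5% level, and the unadjusted comparison of means that underlies the plan's sample size.

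This should be fixed because the remedy is cheap and no planned analysis repairs the rule. It does not invalidate the primary comparison, and the stated sample size reproduces.

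**What to change.** Add to control ineligibility: *any previous hospitalization for COVID-19, or previous COVID-19 ARDS, at any time*. Keep the 12-month rule for other nonelective admissions, and make the Abstract and the opening of Methods agree.

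Add one screening question on earlier COVID-19 admission, and put it to controls already enrolled. Report a sensitivity analysis of the primary and organ-function outcomes that leaves out any enrolled control who breaches the new rule.

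The cost is a small amendment, one question and the loss of a few potential controls. The planned 110 per group stays as it is.
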